### Data Management

The study data will be collected and stored within the REDCap system, which is a web-based, secure, and HIPAA-compliant research management platform. REDCap fully supports several research processes for subject scheduling, subject randomization, data entry and management, as well as data safety monitoring and adverse event reporting. A particular advantage of REDCap is that it leaves a complete audit trail. In addition, the input person is immediately notified if fields are missing and/or out of range values are entered. However, in the case of a loss of Internet access, backup paper copies will be provided, which would then be subsequently entered into REDCap.

Enrolled participants will be identified and queried using REDCap, and no name or other information that would allow a third party to identify a participant directly will be entered into the study database. The data sets stored on a PC will be encrypted and a password will be set to prevent third parties from using the files. Participant identification will be done by numbers or symbols, and the correspondence between these and information that can easily identify the individual (e.g., name, address) to a third party will not be stored in the data set. A list of the correspondence between the information that can be easily identified by a third party (e.g., name, address) shall be stored in a lockable cabinet, etc., (personal information manager: MA).

### Monitoring

The principal investigator will have the institution conduct monitoring to confirm that this research is being conducted properly. In principle, the monitoring report will be submitted once a year.

### Adverse Events

There are no known health or safety risks associated with participation in the described study, and the risk of adverse events is low. Data monitoring will be monitored by the safety monitoring committee. Any minor or major events associated with the intervention or usual care groups will be monitored throughout the duration of the 1-week program. The chief investigators, MA and HA, will review any adverse events or unintended effects detected.

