**Methods:**

This study is a multicenter, exploratory, open cluster-randomized controlled trial. This study will recruit children aged 10–15 years with school refusal. After a 2-week baseline, participants for each cluster will be randomly assigned to one of two groups: with or without mindfulness yoga for 4 weeks. Mindfulness yoga will be created for schoolchildren for this protocol and distributed to the participants on DVD. The primary outcome is anxiety among children with school refusal using the Spence Children's Anxiety Scale-Children.

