### Mindfulness Yoga Program Development

This mindfulness yoga program aims to provide a space and time for children to be able to exist “as they are” to create the psychological place they seek. This mindfulness yoga program is a 4-week program that is done alone at home by watching a mindfulness yoga program video, and the space required for the mindfulness yoga is the size of about a normal exercise mat. Initially, 9 children were given the opportunity to experience the mindfulness yoga program. Feedback was received from the children about the mindfulness yoga program in terms of their time and ability to continue. To make it easier for the participants to continue, one program was set at 20 min or less and the program content changed every week. In the first session, the participants will watch a video in front of the researcher and do the first program. The researcher will instruct them on points such as how to breathe and how to relax. After distribution, the students will be asked to follow the instructions in the video to practice mindfulness yoga (Supplementary Figures 1A–E). Students will also be asked to keep a daily mindfulness yoga diary (Supplementary Figures 2A–D) to track their practice.

The program DVD is structured with the following points in mind:

The program encourages participants to explore their senses and feelings to focus on the state of mindfulness with a non-judgmental awareness of the inner and/or outer experiences, rather than to “do it well” or otherwise perfect the performance.The program starts at a low intensity so that it can be implemented by children with school refusal with low activity intensity. The three major asanas and balance poses of yoga were incorporated by moving the limbs extensively, and the whole body is moved to compensate for the lack of activity.Simple movements that can be safely performed by one person and humming breathing to encourage vocalization were incorporated.

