### Interventions

The study schedule is shown in Figure 1. Group A (Standard care + mindfulness yoga intervention group): After obtaining a 2-week baseline of activity and other data, the participants will perform mindfulness yoga for 28 days. The mindfulness yoga session will be conducted according to a video recording of the instructions. At the time of distribution of the mindfulness yoga video, the participants will perform mindfulness yoga along with the mindfulness yoga video to ensure that the researcher understands the purpose of the activity. After the end of the intervention period, the percentage of days in school will be tracked for 8 weeks. Group B (standard treatment group): After obtaining a 2-week baseline of activity and other data, the participants will continue to measure their activity and other data for 4 weeks. The progress of the percentage of days in school will be followed for another 8 weeks.

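### The Adverse Events section monitors events over a 1-week programme, but the rest of the protocol describes a 4-week (28-day) programme

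*Protocol article*

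**What the plan says.** The Adverse Events section sets the period for event monitoring. It names both arms ("Any minor or major events associated with the intervention or usual care groups") and says that these events "will be monitored throughout the duration of the 1-week program".

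The length of the programme is given in three other places:

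- Abstract, Methods: clusters are randomised to groups "with or without mindfulness yoga for 4 weeks".
- Mindfulness Yoga Program Development: "This mindfulness yoga program is a 4-week program that is done alone at home". The same section says that "the program content changed every week".
- Interventions, Group A: after a 2-week baseline, "the participants will perform mindfulness yoga for 28 days". For Group B over the same period, "the participants will continue to measure their activity and other data for 4 weeks".

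After the intervention period the Interventions section adds a follow-up in which "the percentage of days in school will be tracked for 8 weeks". It also schedules contacts in both groups at the start and at 2, 6 and 14 weeks.

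**The concern.** The adverse event sentence is an operative rule: it tells sites for how long to watch for events. The length it gives belongs to no programme in the article. No other section gives a different adverse event period that could override it. Data Management mentions adverse event reporting only as something the database supports, and Monitoring deals with the conduct of the study and a yearly report.

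A site that followed the sentence to the letter would watch for events only in the first weekly block. The content changes each week and starts at low intensity, so the later blocks contain material that the child has not met in week 1. The article describes researcher supervision only for the first session; after that the child practises at home. Events arising in weeks 2 to 4 would then have no stated collection period in either group, and the comparison of events between groups would rest on the first week alone.

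**Working it through.** **Inputs**

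- Adverse event window as written: 1 week = 7 days (Adverse Events).
- Programme length: 4 weeks (abstract; Mindfulness Yoga Program Development); 28 days (Interventions).
- Baseline 2 weeks, follow-up 8 weeks, contacts at the start and at weeks 2, 6 and 14 (Interventions).
- Primary outcome at Day 29 (Primary Outcome Measures).
- Practice threshold of 20 days (Per Protocol Set).

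**Step 1: does the article's own programme length agree with itself?** 4 weeks × 7 days = 28 days. The abstract, the programme description and the Interventions section agree.

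**Step 2: do other rules fit 4 weeks or 1 week?** The primary outcome at Day 29 falls on the day after 28 days of intervention, so it fits 4 weeks. The per protocol set uses a threshold of 20 days of practice. Daily practice for one week gives at most 7 days, so the threshold could never be reached in a 1-week programme. Both rules fit only the longer length.

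**Step 3: share of the intervention period inside the literal window.** The article does not say on which day the window opens; I take it to open with the intervention.

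- Covered: 7/28 = 25%.
- Not covered: (28 − 7)/28 = 21/28 = 75%.

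This counts scheduled days. Session length is given only as an upper limit, so exposure in minutes cannot be worked out.

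**Step 4: where do the scheduled contacts fall?** Baseline ends at week 2, the intervention ends at week 2 + 4 = 6, and follow-up ends at week 6 + 8 = 14. The week-2 contact is therefore at the end of baseline and cannot pick up events from the yoga period. A 7-day window opening at week 2 closes at week 3, before the next contact at week 6. The week-6 contact comes at the end of the programme and can capture events from the whole period, but only by recall over up to 4 weeks.

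**The case against.** The strongest reply is that this is a wrong numeral and nothing more. The sentence ties monitoring to the duration of the programme, only one programme exists, and it lasts 4 weeks. The sentence that follows has the chief investigators review whatever events are detected, with no time limit. The protocol also rates the risk as low, and sessions last 20 minutes at most. Most of this stands. A reader might infer from the wording that monitoring will stop on day 7 and that three quarters of the exposure will go unobserved. The documents do not support that: the 75% follows from the literal text only. What does not follow is that the text may be left as it is, because it is the only stated window. One could also read it as meaning each weekly block, but the sentence speaks of one programme in the singular, and no section supports that reading.

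Two other inferences are tempting and should not be drawn.

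- **That the trial can no longer meet a stated aim of verifying safety.** The Introduction's aim is to verify usefulness and effectiveness; safe and reliable are adjectives attached to the treatment. No adverse event endpoint is listed among the outcomes.
- **That missing adverse event collection in the 8-week follow-up is an error.** That follow-up is described for tracking school attendance, after the prescribed yoga has ended. No section promises event collection there, so setting the 7 days against the whole period to week 14 uses a denominator that the article never gives for adverse events.

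It can also be said that an article condenses a fuller protocol. That excuses an omission. It does not excuse a stated figure that conflicts with other stated figures.

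**Conclusion.** The article contradicts itself. The adverse event window refers to a 1-week programme, while three sections give 4 weeks or 28 days and two analysis rules fit only that length. Taken literally, the window covers 25% of the intervention days and leaves 75% outside, assuming that it opens with the intervention and that scheduled days are the measure of exposure.

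This is an internal inconsistency, probably a drafting error, and not evidence of a deliberate choice to stop monitoring early. It is worth correcting because it governs safety collection in children practising at home. It is not among the most serious faults a protocol can have: the primary outcome, its analysis, the randomisation and the sample size are unaffected. If the full protocol, which is not shown, already gives the right period, only the article needs correcting.

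**What to change.** Reconcile the Adverse Events section with the abstract, Mindfulness Yoga Program Development and Interventions, so that the adverse event window covers the whole programme period as documented there. State the first and last day of the window and make it identical in both groups.

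The contact already scheduled at week 6 can serve for collection at the end of the period. Say in the text that events from the preceding weeks are then gathered by recall. The week-2 contact cannot serve this purpose.

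Whether the window also runs into the 8-week follow-up, with collection at the week-14 contact, is optional. The sponsor should state it either way, since replacing the numeral alone would leave that question open.

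The cost is a one-line correction and no added visits.

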### Patient and Public Involvement

In order to develop this yoga program, we asked children between the ages of 10 and 15 for their opinions on whether the program content and time would allow them to continue every day.In preparing the informed assent document, we asked children between the ages of 10 and 15 for their opinions on whether they could read the text and whether the content was easy to understand.Citizen members participated in the ethical review board of Kagoshima University and exchanged opinions.

## Discussion

For this study, we developed a mindfulness yoga program and protocol, and examine whether mindfulness yoga can improve anxiety in children with school refusal. Our mindfulness yoga program was developed based on the opinions of children of the same age, and is a program that children can continue to do every day without getting bored.

This study has several strengths. First, it is a new yoga program that combines mindfulness and yoga. Second, this is incorporation of cluster randomization, in which schools and affiliations are randomized as clusters. Third, the content of mindfulness yoga program and time designed as sustained without burden by incorporating children's opinions in the study design. Fourth, because it is a video-based intervention, it can be used in a variety of settings, the ability to implement mindfulness yoga in schools and homes without being limited by geographical factors, since the video-based intervention allows mindfulness yoga to be implemented without direct instructor contact.

The study also has several limitations. First, the analysis design does not include social backgrounds that may contribute to truancy, such as parent-child relationships, economic problems, and friendships. Second, the study does not include developmental disabilities other than intellectual disabilities as the exclusion criteria. Third, the seasonal variation of school refusal was not considered in the intervention design or data collection.

To our knowledge, little research on mindfulness-yoga intervention for children with school refusal has been conducted. Our proposed study is the first RCT intervention for the children with school refusal to be implemented. If this study shows positive results, it will be possible to recommend that mindfulness yoga be implemented with similar strategies with other children and beyond. In addition, the use of mindfulness yoga programs that can be implemented at home or at school may promote cooperation between the fields of medicine and education, and provide comprehensive and integrated support for school children. In this way, we believe that we can contribute to the smooth implementation of support to reduce the anxiety of children with school refusal, and to the reduction of the number of children who refuse to go to school.

## Ethics Statement

The studies involving human participants were reviewed and approved by Kagoshima University (IRB No: 190263).

